## Abstract

**Background:**

Mild traumatic brain injury (mTBI) is an acknowledged public health problem. Up to 25% of adult with mTBI present persistent symptoms. Headache, dizziness, nausea and neck pain are the most commonly reported symptoms and are frequently associated with cervical spine and vestibular impairments. The most recent international consensus statement (2017 Berlin consensus) recommends the addition of an individualized rehabilitation approach for mTBI with persistent symptoms. The addition of an individualized rehabilitation approach including the evaluation and treatment of cervical and vestibular impairments leading to symptoms such as neck pain, headache and dizziness is, however, recommended based only on limited scientific evidence. The benefit of such intervention should therefore be further investigated.

**Objective:**

To compare the addition of a 6-week individualized cervicovestibular rehabilitation program to a conventional approach of gradual sub-threshold physical activation (SPA) alone in adults with persistent headache, neck pain and/or dizziness-related following a mTBI on the severity of symptoms and on other indicators of clinical recovery. We hypothesize that such a program will improve all outcomes faster than a conventional approach (between-group differences at 6-week and 12-week).

**Methods:**

In this single-blind, parallel-group randomized controlled trial, 46 adults with subacute (3 to12 weeks post-injury) persistent mTBI symptoms will be randomly assigned to: 1) a 6-week SPA program or 2) SPA combined with a cervicovestibular rehabilitation program. The cervicovestibular rehabilitation program will include education, cervical spine manual therapy and exercises, vestibular rehabilitation and home exercises. All participants will take part in 4 evaluation sessions (baseline, week 6, 12 and 26) performed by a blinded evaluator. The primary outcome will be the Post-Concussion Symptoms Scale. The secondary outcomes will be time to clearance to return to function, number of recurrent episodes, Global Rating of Change, Numerical Pain Rating Scale, Neck Disability Index, Headache Disability Inventory and Dizziness Handicap Inventory. A 2-way ANOVA and an intention-to-treat analysis will be used.

**Discussion:**

Controlled trials are needed to determine the best rehabilitation approach for mTBI with persistent symptoms such as neck pain, headache and dizziness. This RCT will be crucial to guide future clinical management recommendations.

**Trial registration:**

ClinicalTrials.gov Identifier - NCT03677661, Registered on September, 15th 2018.

## Background

Mild traumatic brain injury (mTBI) is an acknowledged public health problem. It is estimated that between 1.6 to 3.8 million brain injuries occur annually in the United States, with up to 75% classified as mild [1]. The majority of mTBI resolves within 10 to 14 days [2–5]. However, up to 31% of pediatric cases [6] and 25% of adult cases [5, 7] present post concussive syndrome (PCS), which is a persistence of somatic (for example: headache, neck pain, dizziness, nausea, balance dysfunction) [8, 9], cognitive (for example: memory loss and slowed reaction time) [10], and/or psychological (for example: depression and anxiety) [10, 11] symptoms [12]. Among these symptoms, headache and dizziness are the most commonly reported, followed by nausea and neck pain [2, 5, 9]. Many of these PCS symptoms could be explained by injuries to structures near or in the head, other than the brain itself. For example, following a trauma, structures such as the cervical spine, the vestibular ocular system and the temporomandibular joint can be injured. The energy needed to produce an mTBI can be transferred to the neck and produce an injury mechanism similar to the one observed in whiplash associated disorders (WAD). Neck pain, headaches, dizziness and balance dysfunction are common symptoms associated with both mTBI and WAD [5, 13, 14]. Specific interventions aimed at addressing the different underlying cause of these symptoms could lead to improved outcomes. For individuals presenting with PCS, the most recent international consensus statement (2017 Berlin consensus on concussion in sport) [5] recommends the addition of an individualized rehabilitation approach to a sub-threshold physical activation (SPA) strategy. However, this new recommendation is based on limited scientific evidence as well as expert recommendations [5]. Therefore, the effects of adding individualized rehabilitation interventions for the treatment of potential impairments of body function associated with neck pain, headache and dizziness, [5] needs to be evaluated in individuals with mTBI. Several systematic reviews [15–18] have shown that multimodal rehabilitation interventions and vestibular rehabilitation improved function for participants with neck pain, cervicogenic headache, dizziness and balance dysfunction over control. None of the randomized control trials (RCT) studied in these reviews, however, included individuals with mTBI [15–18]. Two RCTs have partially looked at the effects of rehabilitation interventions in some subgroups of mTBI patients. One RCT [19] (*n* = 31) demonstrated that patients with sport-related concussion treated with a standardized combination of vestibular and cervical physiotherapy were quicker to be medically cleared to return to sport than a control group who rested before gradually returning to activities. However, the intervention used in that study did not include an individualized SPA program. Another RCT [20] recruited 41 sport-related concussion patients with dizziness as the main symptom. Participants were quicker to be medically cleared in the rehabilitation treatment targeting dizziness than in the minimal intervention group (subtherapeutic and non-progressive therapeutic techniques). However, due to the multi-factorial nature of mTBI, treatment must be individualized to the patient’s clinical presentation and environment and the outcomes need to encompass all types of symptoms. In that context, there is a need for further RCTs evaluating the effect of an individualized SPA combined with cervicovestibular rehabilitation program (based on the Berlin consensus) on mTBI compared to an individualized SPA alone.

### Objectives and hypothesis

The primary objective of the current RCT is to compare the addition of a 6-week individualized gradual SPA program combined with cervicovestibular rehabilitation program to a gradual SPA program alone in adults with subacute (> than 3 weeks post mTBI) headache, neck pain and /or dizziness-related to mTBI on the severity and impact of symptoms as measured by the Post-Concussion Symptoms Scale (PCSS). The secondary outcomes will be: time for clearance to return to usual activities, number of recurrence episode within 26 weeks after the treatment phase, functional level, intensity of neck pain, headache and dizziness. As SPA is well recognised for the treatment of persistent PCS [5], it supports the choice of using SPA as the comparator intervention in the present study. Our hypothesis is that the individualized SPA combined with cervicovestibular rehabilitation program will improve overall symptoms, time to return to activities as well as function faster and to a greater extent than the conventional approach and between group differences will be observed at week 6 and 12.

## Methods

### Study design

This single-blind, parallel-group RCT will include 8 supervised treatments during a 6-week rehabilitation program and four evaluation sessions over 26 weeks (baseline, week 6 [immediately after the rehabilitation program], week 12 [6 week after the end of the rehabilitation program] and week 26). All participants will take part in the baseline evaluation. After giving informed consent, they will first complete a questionnaire on sociodemographic (age, gender, type of sport or physical activities, number of years playing sport and/or other activities), symptomatology (mechanism of injury, history of previous mTBI, history of dizziness, headache, neck pain and unsteadiness) and comorbidity, as well as self-administered questionnaires that evaluate symptoms and functional limitations, including the PCSS (primary outcome). Once baseline data are collected, participants will be randomly assigned to a control or an experimental group. The control group will receive a 6-week gradual sub-threshold physical activation (SPA) program. The experimental group will receive a gradual SPA program combined with a cervicovestibular rehabilitation program. Between week 6 and week 12, participants will be asked to continue their exercises and follow the advice given at the last meeting with the health professional. Six, 12 and 26 weeks after randomization, all the outcomes will be revaluated (see Table 1). The evaluation sessions will be carried out at the *Centre interdisciplinaire de recherche en réadaptation et en intégration sociale* (CIRRIS) by a research assistant blinded to group assignment, while the interventions will be given at *Clinique Cortex* by experienced physiotherapists, neuropsychologists and kinesiologists. Recruitment began on April 1st 2019 in Quebec City, Canada. See Table 1 for Schedule of enrolment, interventions, and assessments. Ethics approval has been obtained from the Sectorial Rehabilitation and Social Integration Research Ethics Committee of the CIUSSS-CN (#2018–619)*.* The study protocol has been registered on ClinicalTrials.gov [NCT03677661–09/15/2018 - version 1].

**Table 1 Tab1:**
[figure not shown]
Schedule of enrolment, interventions, and assessments

t_1_ = First intervention session post-allocation, t_2_ = week 6, t_3_ = week 12, t_4_ = week 26. *SPA* Sub-threshold Physical Activity, *SPSS* Post-Concussion Symptoms Scale, *NPRS* Numerical Pain Rating Scale, *NDI* Neck Disability Index, *DHI* Dizziness Handicap Inventory, *HDI* Headache Disability Index, *GRC* global rating of change

### Population

Forty-six adults with a diagnosis of mTBI (based on the definition of McCrory et al.) [5] and symptoms of dizziness, neck pain and/or headaches (reported on the PCSS) [21] lasting for more than 3 weeks will be recruited. Sample size calculation is based on changes evidenced by the PCSS for individuals with mTBI. According to sample size calculation (G*Power 3.1.9.2; α = 0.05, effect size = 0.8, power [1-β] = 0.80, SD = 20.0 PCSS points, MDC = 12.3 PCSS points [22], 10% attrition), a minimum of 23 subjects is needed in each group. The expected attrition (10%) is based on the drop-rate in previous RCT from our group [23–26] and is more than the observed drop-out in similar studies in this population (6% [19] and 2% [20]). Therefore, 46 participants with mTBI will be recruited. Potential participants will be recruited at *Clinique Cortex* (an interdisciplinary concussion clinic specialized in the management of mTBI; 500 new patients with mTBI are evaluated every year), in medical clinics around Quebec City, and through the electronic mailing list of the students and employees at *Université Laval* (> 52,000 individuals).

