### The primary outcome measure

#### *Post-Concussion Symptoms Scale (PCSS)*

The severity and impact of symptoms will be measured by a self-reported scale, the PCSS [41]. This scale is a list of 22 symptoms for which participant rate each symptom for severity on a 0 (none) to 6 (severe) numerical scale. The maximum possible score is 132 (22 × 6 = 132). This valid and reliable scale has a minimal detectable change (90% confidence interval) of 12.3 PCSS points [22]. Normative values have been established [41]. The symptoms list can be divided in four main sub-groups (physical, cognitive, emotional and sleep disorders) and analysed accordingly [5].

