### Statistical analyses

Descriptive statistics will be used for all outcome measures at each measurement time to summarize results. Baseline demographic data will be compared (independent *t*-test and Chi-squared tests) to establish the comparability of groups. All data will be tested to check the distributional assumptions for the inferential statistical analyses. An intention-to-treat analysis will be used in which all participants will be analysed in the group to which they were originally assigned. Per protocol analysis will also be performed. All dropouts and the reason for dropping out of the study will be reported. Any harm or unintended effects during the programs will be recorded. A 2-way ANOVA (2 Groups [Group 1 or 2] × 4 Time [week 0, 6, 12, 26]) will be used to analyse the effects of the rehabilitation programs on the primary outcome and on most of the secondary outcomes (SPSS 22, proc. GENLIN). We expect no group effects, as the groups should be equal at baseline. A time effect should be observed, as both groups should improve given they will both receive an interventions. Finally, we expect a significant Time x Group interaction since the groups should react differently over time, ***with a faster recovery for the Experimental group mainly seen at week 6 and 12***. This will be statistically detailed with post-hoc tests (Bonferroni correction). An independent t-test will be used to analyse the effects of the rehabilitation programs on clearance to return to function.

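### The sample-size inputs do not agree (12.3/20 is 0.615, not 0.8), and 23 per group does not give the stated 80% power in a two-sided two-group t-test on either reading of the target

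*Protocol article*

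**What the plan says.** The sample-size statement is in the protocol article, Methods, Population. It names G\*Power and sets alpha at 0.05, then gives "effect size = 0.8, power [1-β] = 0.80, SD = 20.0 PCSS points, MDC = 12.3 PCSS points" together with 10% attrition. The result is that "a minimum of 23 subjects is needed in each group", so 46 will be recruited. The Randomisation/blinding section plans two equal groups of 23. Neither section states the test family, the sidedness of alpha, or a correlation between repeated measurements.

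The section on the Post-Concussion Symptoms Scale (PCSS) describes the 12.3 figure as a "minimal detectable change (90% confidence interval) of 12.3 PCSS points", that is, a measurement property of the scale. Nowhere is it called the difference the trial aims to detect.

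The Statistical analyses section plans a 2 (group) by 4 (time) ANOVA for the PCSS. It expects the benefit to appear in the time-by-group interaction, chiefly at weeks 6 and 12, and follows this with Bonferroni-corrected post-hoc tests. It mentions no one-sided test.

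**The concern.** Effect size, SD and a difference in points are three expressions of two quantities: once two are fixed, the third follows. Here all three are listed and they do not match. A reader cannot tell whether the trial was sized for 12.3 points or for 16. The stated 23 per group also looks too small for a conventional two-sided comparison at 0.8.

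What is at stake is how the result is read. If the trial is described as having 80% power and does not have it for the difference the reader has in mind, a non-significant result can be taken as stronger evidence against the added cervicovestibular programme than the data warrant.

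**Working it through.** **Inputs stated in the Population section:** alpha 0.05 (sidedness not given), d = 0.8, power 0.80, SD 20.0, MDC 12.3, attrition 10%, 23 per group.

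**Step 1. Do the inputs agree?**
- 12.3 / 20.0 = 0.615
- 0.8 × 20.0 = 16 points
- 12.3 / 0.8 = 15.4, the SD that would be needed for 0.8 to correspond to 12.3 points

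**Step 2. Reproduce 23 per group.** The normal approximation is n per arm = 2(z_alpha + z_beta)² / d². The exact version uses the noncentral t distribution.

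Two-sided, d = 0.8:
- Normal: 2 × (1.960 + 0.842)² / 0.64 = 24.5
- Exact: 25.5, so 26; with attrition 26/0.9 = 28.9, so 29. This is not 23.

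One-sided, d = 0.8:
- Normal: 2 × (1.645 + 0.842)² / 0.64 = 19.3, so 20; 20/0.9 = 22.2, so 23.
- Exact: 20.03; 20.03/0.9 = 22.3, so 23. Rounding to 21 first gives 21 × 1.1 = 23.1, or 21/0.9 = 23.3, which rounds up to 24.

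d = 0.615, exact:
- Two-sided: 43 per arm, 48 with attrition
- One-sided: 34 per arm, 38 with attrition. Neither is 23.

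The stated 23 can also be reached without a one-sided test. A repeated-measures between-groups F test with f = 0.4 (d = 0.8), two measurements and correlation 0.5 needs 20 per arm (20/0.9 = 22.2, so 23). With three or four measurements and correlation 0.7 it needs 21 (21 × 1.1 = 23.1). These correlations are assumptions; the article gives none. That F test also addresses the group main effect, whereas the Statistical analyses section expects the effect in the interaction. The corresponding interaction F test at f = 0.4 needed at most 10 per arm (12 with attrition) over two to four measurements and correlations of 0.3 to 0.8, so it does not explain 23.

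**Step 3. Power delivered by 23 per group.** After 10% attrition, 23 × 0.9 = 20.7, taken as 21. Unadjusted two-sided t-test at 0.05, exact:

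| Target difference | d | 21 per arm | 23 per arm |
|---|---|---|---|
| 16 points | 0.8 | 72% | 76% |
| 12.3 points | 0.615 | 49% | 53% |

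**Step 4. Difference detectable with 80% power.** At 21 per arm the exact calculation gives d = 0.886, and 0.886 × 20 = 17.7 points.

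**Step 5. Effect of baseline adjustment.** Adjusting for baseline multiplies the SD by √(1 − r²), where r is the baseline to follow-up correlation. No r is given, so values are assumed. At 21 per arm:

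| Assumed r | Detectable difference | Power, 16 points | Power, 12.3 points |
|---|---|---|---|
| 0 | 17.7 | 72% | 49% |
| 0.5 | 17.7 × 0.866 = 15.3 | 83% | 61% |
| 0.7 | 17.7 × 0.714 = 12.7 | 94% | 78% |

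**The case against.** The best defence is that 12.3 was never the target. The article labels it an MDC and describes it as a property of the scale. The explicit effect size is 0.8, which with SD 20.0 means 16 points. That exceeds the MDC, so 12.3 may be listed only for reference. This reading is possible, and on it the inputs are unexplained rather than strictly contradictory. It does not rescue the power statement: an unadjusted two-sided t-test for 16 points has 72% to 76% power, still short of 80%.

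A second defence is that the planned analysis uses the baseline and three follow-ups, so a single-visit t-test understates its power. This also stands in part. At an assumed correlation of 0.5, power for 16 points rises to 83%. But the claim then depends on a figure the article does not give, and for 12.3 points with 21 per arm even a correlation of 0.7 leaves power at 78%.

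Three stronger readings are tempting, and the document does not support them:
- A reader might infer that a one-sided test was used. It is one route to 23, but step 2 shows others, and the article does not say which calculation was run.
- A reader might infer that the trial's true power is about 49%. That holds only if 12.3 points is the target and the test is an unadjusted two-sided t-test at one visit.
- A reader might lower the power further by spreading the Bonferroni correction over all four visits. The plan applies the correction to post-hoc tests that detail the interaction and does not say how many there are. One of the four visits is baseline, where no treatment effect can exist.

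**Conclusion.** The point holds in a conditional form. The effect size, SD and MDC listed for one calculation are inconsistent, or at best unexplained, and the stated 80% does not follow from them under a two-sided two-group t-test. The shortfall is 4 to 8 percentage points if the target is 16 points (76% with no dropout, 72% with 21 per arm) and 27 to 31 points if it is 12.3 (53% and 49%).

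These sizes assume an SD of 20.0, alpha 0.05 two-sided, one unadjusted comparison of two means, and attrition of zero or 10%. Two-sidedness is itself an assumption: the article does not state it, but declares nothing else. Baseline adjustment could restore 80% for 16 points if the correlation were about 0.43 or higher, since √(1 − (0.8/0.886)²) = 0.43. The document neither claims nor supports such a value.

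**What to change.** Keep 46 participants and amend the Population section:

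1. State one target difference in PCSS points, with its SD, the test, and alpha 0.05 two-sided. Make the effect size agree: either 16 points with d = 0.8, labelling 12.3 as a reference MDC only, or 12.3 points with d = 0.615.
2. Replace the 80% claim with what 46 randomised participants deliver. With about 21 completers per arm, that is 80% power for about 17.7 points unadjusted. With baseline adjustment it is about 15.3 or 12.7 points if the correlation is assumed to be 0.5 or 0.7; name the assumed correlation and its source.
3. If the calculation actually run was one-sided or used a repeated-measures model, say so and give the missing inputs.
4. Tie the power statement to one primary contrast, and say that a null result will be read through its confidence interval.

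The cost is a wording amendment and a less favourable stated power. No extra patients are needed. Recruitment began in April 2019 according to the Study design section, so the amendment should be dated and described as a restatement of the original calculation.

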#### *Inclusion criteria*

Between 18 and 65 years of age;Sustained a mTBI in the past 3 to 12 weeks;Having ongoing post-concussion symptoms from the list in the PCSS that started 72 h or less after an impact;Having felt at least one or more of the following cognitive symptoms: lost of consciousness for less than 30 minutes following the trauma, feeling slowed down, feeling like in a fog, “don’t feel right”, difficulty concentrating, difficulty remembering and confusion that started 72 h or less after an impact;Having abnormalities on one of the following tests: the cervical physical examination (eg, tenderness/spasm/pain on segmental testing, or reduced motion), the vestibular evaluation (eg, Dix halpike test, vestibulo-ocular reflex test, or head thrust test) or the ocular motor evaluation (eg, convergence, smooth visual pursuits, or saccades).

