### Randomisation/blinding

A randomisation list will be generated by an independent research assistant (not involved in data collection) prior to the initiation of the study using a random number generator. Allocation will be concealed in sealed and opaque envelopes that will be sequentially numbered. A blocked randomisation will be used to make sure that two equal groups of 23 participants are obtained. Stratification will be done according to sex to ensure women and men are equally represented in each group as it has been shown that women tend to recover more slowly than man from a mTBI [6, 27]. Given that it is not possible to blind the treating physiotherapist and the participants, a single-blind design will be used as only the evaluator will be blinded. One of the Principal Investigator (PI) will open the randomisation envelope indicating the participant’s assignment and will send the information to the treating therapist. The physiotherapists, neuropsychologists and the kinesiologists will be blinded to the baseline evaluation results. To evaluate the effectiveness of blinding, the evaluator will answer the following question at the week-6 evaluation: *“In your opinion, which intervention did this participant received?”* The possible answers are: 1) SPA program (control group); 2) SPA combined with cervicovestibular rehabilitation program (experimental group); 3) I have no idea. Participants will be unaware of the treatment provided to the participants in the other group. Evaluation will be done in a separate site than the intervention site and participants will be instructed not to reveal or discuss treatment with the evaluator.

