#### Clearance to return to function

The number of days between the initial evaluation, the date of the trauma and the full clearance to return to function (work, study or physical activity/sport) will be measured. The clearance to return to function will be determined by the treating therapist and the neuropsychologist. The treating therapist (physiotherapist or kinesiologist according to which group the patient will be allocated to) will use the stepwise progression from the 5th International Consensus Statement on Sport Concussion [5]. As patients achieve the last step of this progression, indicating that the patient can safely return to play, the neuropsychologist and the kinesiologist will confirm this decision with a structured interview (neuropsychologist) and an ergocycle aerobic test (kinesiologist). The clearance will be determined by the day for which 1) the symptoms will have return to usual level 2) the neurological, cervical spine and vestibular impairments found at the beginning of the study will be considered in the normal range by the treating therapist 3) the subject returned to his normal level of all functional activities.

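### The stated PCSS and clearance analyses leave out sex (the stratification factor) and time since injury (3 to 12 weeks at entry), and clearance is given two starting dates

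*Protocol article*

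**What the plan says.** All of this is in the Methods of the Protocol article.

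- **Inclusion criteria.** Eligible patients "Sustained a mTBI in the past 3 to 12 weeks", that is 21 to 84 days before entry.
- **Randomisation/blinding.** "Stratification will be done according to sex to ensure women and men are equally represented in each group". The reason given is prognostic: "it has been shown that women tend to recover more slowly than man from a mTBI". No other stratification factor is named.
- **Statistical analyses.** For the primary outcome and most secondary outcomes, "A 2-way ANOVA (2 Groups [Group 1 or 2] × 4 Time [week 0, 6, 12, 26]) will be used". The treatment effect is looked for in the Time by Group interaction, "with a faster recovery for the Experimental group mainly seen at week 6 and 12". For clearance, "An independent t-test will be used to analyse the effects of the rehabilitation programs on clearance to return to function". Neither analysis names a covariate.
- **Clearance to return to function.** The outcome is "The number of days between the initial evaluation, the date of the trauma and the full clearance to return to function". This gives two starting dates, and the Statistical analyses section does not say which one the t-test uses.

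**The concern.** The trial's hypothesis is about speed of recovery. Its authors treat sex as a predictor of that speed and stratify on it, but the stated analyses then do not use it. If sex predicts outcome, stratification lowers the true variance of the treatment comparison, and an analysis that omits sex does not collect that gain.

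Time since injury varies fourfold at entry. It is known for every patient, because eligibility depends on it and the clearance outcome uses the injury date. It is neither stratified nor adjusted for, so with 23 patients per arm a chance difference between arms goes uncorrected.

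For clearance the point is sharper. Counted from trauma, the interval before the initial evaluation is itself part of the outcome. Treatment cannot change it, and any arm difference in it passes into the result day for day. Because the text leaves the starting date open, one t-test can be run in two ways that give different answers.

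**Working it through.** **Inputs from the Protocol article.** Entry window 3 to 12 weeks; 23 per arm; 10% attrition; PCSS SD 20.0; minimal detectable change (MDC) 12.3.

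**Assumptions, because the article gives no figure.** Uniform entry over the window; correlation r between time since injury and follow-up PCSS; SD of days from initial evaluation to clearance.

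**The article's own figure.** One-sided α = 0.05, effect size 0.8 and power 0.80 give 20 per arm by the normal approximation, and 20/0.9 = 22.2, so 23. A two-sided test does not give 23. That is a separate matter; here 23 per arm serves only as an input.

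**1. Chance imbalance.** Uniform on 3 to 12 weeks: SD = 9/√12 = 2.60 weeks = 18.2 days. SE of the arm difference in means = 2.60 × √(2/23) = 0.77 week. The 95% range is about ±1.5 weeks. P(difference above 1 week) = 2 × [1 − Φ(1/0.766)] = 0.19.

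A one-SE imbalance is √(2/23) = 0.295 SD. At a single follow-up visit it would shift the PCSS difference by r × 20 × 0.295, which is 1.2, 1.8 or 2.4 points at r = 0.2, 0.3 or 0.4, against an MDC of 12.3.

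**2. Precision for PCSS at one visit (ANCOVA).** With about 20 evaluable per arm there are 40 − 2 = 38 residual degrees of freedom. The variance ratio after adding one covariate is about (1 − r²)(1 + 1/38).

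| r | Variance ratio | Equivalent gain in patients |
|---|---|---|
| 0.2 | 0.96 × 1.026 = 0.985 | 1.5% |
| 0.3 | 0.91 × 1.026 = 0.934 | 7% |
| 0.4 | 0.84 × 1.026 = 0.862 | 16% |

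Break-even is at r² = 1/39, so r ≈ 0.16. The most that can be lost, at r = 0, is 1/38 = 2.6% in variance.

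**3. What a covariate does in the stated 2 × 4 model.** Week 0 is a level of Time, so the Group by Time test compares changes from week 0 within each person. Let a person-level covariate w enter with coefficient γ as a main effect. In the change from week 0 to week t it contributes γw − γw = 0. With complete data, the interaction estimates and their standard errors are therefore unchanged. The same applies to sex. Only covariate-by-time terms, or moving week 0 from outcome to covariate, can alter the treatment test. The figures in step 2 belong to the second kind of analysis.

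**4. Clearance.** Days from trauma = days from initial evaluation + entry delay. If the delay has SD 18.2 and is independent of the rest, the inflation in required sample size is (s² + 18.2²)/s².

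| s, SD from initial evaluation (assumed) | Inflation | Extra patients |
|---|---|---|
| 20 days | 731/400 = 1.83 | 83% |
| 30 days | 1231/900 = 1.37 | 37% |
| 40 days | 1931/1600 = 1.21 | 21% |

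If the exact delay is a linear covariate, the two versions of the outcome differ only by that covariate. The estimated group effect is then identical from either starting date.

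**The case against.** - **Randomisation already protects the comparison.** This stands. A reader might infer from the wide window that the treatment comparison is biased. The documents do not support that: allocation is random and concealed, so the issue is precision and chance imbalance.
- **The article does not show that time since injury matters in these patients.** This stands in part. The Background says most mild injuries resolve within 10 to 14 days, but this trial enrols only people still symptomatic after 3 weeks. No section says recovery differs between week 3 and week 12 in persistent cases, so every r above is an assumption. For sex the article does state a prognostic role.
- **Adding a covariate leaves the stated primary test unchanged.** This stands for a main effect (step 3). It is tempting to read the 1.5% to 16% as a gain in the planned interaction test, but those figures hold only for an ANCOVA at one visit. Week-0 PCSS already removes stable differences in level, so in the planned model the relevant correlation would be with change in PCSS.
- **Covariates are commonly left to an analysis plan that is not shown.** A missing list would be no finding. But the article fixes the model with week 0 as an outcome level, fixes an independent t-test (which takes no covariate), and defines clearance with two starting dates. Those are stated choices.
- **The clearance penalty presumes counting from trauma.** This stands. The article names the initial evaluation first and does not say which date is tested. The 21% to 83% is what the trauma date would cost, and it would shrink if longer delay went with quicker later recovery.
- **A second stratification factor would thin the strata at 46 patients.** This stands, and none is needed.

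**Conclusion.** The point holds as one of efficiency and clear definition. The stated analyses leave out the trial's own stratification factor and a widely varying entry characteristic that is already recorded, and clearance has no single starting date.

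For PCSS the size is uncertain. It is negligible at r of 0.2 or below, a trivial loss below about 0.16, and worth 7% to 16% more patients at r of 0.3 to 0.4, provided the analysis is one in which the covariate can act. Under uniform entry, a 1-week imbalance or more is a 19% event.

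The clearance limb is stronger in kind, because the delay before entry is arithmetically part of a count from trauma. It is conditional on that date being the one tested, on the assumed SDs of 20 to 40 days, and on independence. The documents support neither a claim of bias nor a claim that the planned PCSS interaction test loses a known amount of power.

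**What to change.** **PCSS.** Analyse weeks 6, 12 and 26 in a repeated-measures model, with baseline PCSS, sex and weeks since injury as pre-specified covariates and week 0 as a covariate, not an outcome level. The treatment test is then the group difference at the named weeks; the interaction among the three follow-up weeks would not serve. Alternatively, keep week 0 as an outcome and add sex-by-time and weeks-since-injury-by-time terms. Adding main effects alone would not change the Group by Time test.

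**Clearance.** State one starting date for the test, the initial evaluation. Replace the unadjusted t-test with a comparison adjusted for weeks since injury and sex. Report days from trauma descriptively.

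**Cost.** Wording in the analysis section and the outcome definition, settled before group data are seen. It needs no new data and no change to randomisation. It uses one degree of freedom per covariate in the first PCSS option and in the clearance model. In the second PCSS option each covariate adds three more for its interaction with four time points.
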